#### 8.5. Analysis of secondary hypothesis H3

The analysis of secondary hypothesis H3 will have the respective scores of the SRS-22r questionnaire as the dependent variable and the type of brace worn as the independent variable. The 95% confidence interval of the difference in score between the test brace and the control brace will be constructed and compared to the non-inferiority margin.

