## 4. Objective and assumptions

**The general objective** of the project is to validate the new CAD/CAM brace design method integrating the optimization of immediate correction.

**Primary Hypothesis (H1)** : After 1 year and 2 years of use, the out-of-brace correction, as measured by Cobb's angle, from the Test braces will be non-inferior to the Control braces. The non-inferiority margin will be 5 degrees.

**Secondary hypothesis (H2)** : The immediate and medium-term (1 and 2 years) failure rate of treatment will be 10% lower for Test braces compared to Control braces. There are three different types of failures:

1. Mid-term failure (1 and 2 years) – relative progression : A progression of the out-of-brace Cobb angle of 5 degrees or greater than the value measured at visit 1.
2. Intermediate (study duration) failure – absolute progression : A progression of the Cobb angle of the main off-brace curvature to greater than 45 degrees (SRS failure criterion).
3. Medium-term failure (duration of the study) – surgery : Stopping treatment with a brace and a decision to have surgery (AVBGT or fusion).

**Secondary hypothesis (H3)** : The quality of life of patients wearing Test braces in the medium term, as measured with the SRS-22r questionnaire, will be non-inferior to that of patients wearing control braces. The non-inferiority margin will be 10%.

**Secondary hypothesis (H4)** : The immediate in-brace correction of the Cobb angle of the Test brace will be no less than that of the control brace. The non-inferiority margin will be 5 degrees.

The effects measured (dependent variables) are as follows:

| Effects measures                                                         | Descriptions                                                                           |
|--------------------------------------------------------------------------|----------------------------------------------------------------------------------------|
| Major                                                             |                                                                                        |
| Cobb angle off brace (Initial, 6 months, 1 year, 2 years).               | Measure using low-dose EOS radiography to assess the evolution of scoliosis.           |
| Secondary                                                         |                                                                                        |

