| Cobb angle in the brace. (Initial)                                       | Measure using digital radiography to assess the immediate corrective effect of braces. |
| Treatment failure rate (Initial, 6 months, 1 year, 2 years)              | See failure criteria in section 6.5                                                    |
| The lordosis and kyphosis effect of the brace (Initial, 1 year, 2 years) | The angles of the curves in the sagittal plane will be measured on the x-ray images.   |
| The number of hours wearing the brace per day (Initial, 1 year, 2 years) | A compliance monitor will measure the rate of brace use.                               |
| The patient's quality of life (Initial, 6 months, 1 year, 2 years)       | The quality of life of patients will be calculated from the SRS-22r questionnaire      |

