## 6.4. Method and follow-up visits

### **Visit 1: Acquisition of parameters**

During the initial visit, the following interventions will be performed :

- An EOS low-dose digital biplanar radiograph (EOS-Imaging, Paris, France) will be acquired: simultaneous AP and lateral while the patient is standing in a comfortable position, with hips and knees extended, both elbows bent with the hands at the side of the head. A student will digitize the anatomical landmarks on each x-ray, so as to obtain a 3D reconstruction of the spine, pelvis and rib cage. A scanning technician, blind to the purposes of our study and the subject's allocation group, will verify and approve each of the reconstructions. The relevant geometric variables will be obtained automatically on

Clindexia, eliminating any possibility of radiological measurement bias by a human observer.

- Curve flexibility will be qualitatively assessed by the orthopedist to determine if the patient has a flexible, normal, or rigid curve
- A scan of the external surface of the trunk will be acquired with the TechMed3D surface scanner.
- The SRS-22r questionnaire will be administered. This questionnaire is administered to patients in the scoliosis clinics at the CHU Sainte-Justine even if they are not part of a research project at all visits (except for the delivery of a brace). The questionnaire is administered through the AMIKO platform (platform developed by the CHU Sainte-Justine to computerize the questionnaires at the orthopedic clinic), or the questionnaire is administered in paper version.

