### **Design and manufacture of braces**

Before the second visit, which will take place approximately one month after the first, each patient will have a control brace and a test brace designed and manufactured according to the specific geometry of their trunk and spine as described in Section 5.

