## 8. Statistical analysis plan

### 8.1. Sample size justification

The sample size was calculated to be able to accept the main hypothesis (H1) with a probability of 5% of committing the type I error and a power of 80%. The calculation was performed with nQuery software (GraphPad Software DBA Statistical Solution, San Diego, CA) and the following parameters were used:

- Significance level  $\alpha = 5\%$
- Allocation ratio  $k = 1$
- Margin of non-inferiority  $\delta = 5^\circ$
- standard deviation  $\sigma = 7^\circ$ 
- Power  $(1 - \beta) = 80\%$

The sample size should be 25 per group, so a total of 50 patients. On the other hand, a loss to follow-up of 15% is anticipated. We will therefore need 29 patients per group for a total of 58 patients.

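### The quality-of-life comparison (H3) names brace type as its only independent variable and leaves out the SRS-22r score collected at Visit 1, which widens the confidence interval and leaves chance baseline imbalance in the estimate

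*Protocol*

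**What the plan says.** - **Hypothesis (section 4).** H3 claims non-inferiority against the control brace with a margin of 10%: "The quality of life of patients wearing Test braces in the medium term, as measured with the SRS-22r questionnaire, will be non-inferior". The base of that percentage is not stated.
- **Analysis (section 8.5).** The analysis "will have the respective scores of the SRS-22r questionnaire as the dependent variable and the type of brace worn as the independent variable". Then: "The 95% confidence interval of the difference in score between the test brace and the control brace will be constructed", to be compared with the margin. No baseline covariate and no change from baseline is named.
- **Baseline measurement (section 6.4, Visit 1).** "The SRS-22r questionnaire will be administered". The effects table in section 4 lists the initial assessment first: "The patient's quality of life (Initial, 6 months, 1 year, 2 years").
- **Timing (section 6.4).** The braces come later than this questionnaire: "Before the second visit, which will take place approximately one month after the first, each patient will have a control brace and a test brace". The Visit 1 score therefore precedes any study brace.
- **Randomisation and size (sections 7 and 8.1).** Allocation is 1:1 in blocks of 2, 4 or 6, with no stratification factor mentioned. The sample size is 25 per group, raised to 29 for loss to follow-up, and is calculated for H1 only.

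**The concern.** Answers to the same questionnaire from the same patient before and during treatment will usually be correlated. A comparison of follow-up scores by brace type alone leaves the stable between-patient part of the variation in the error term, so the interval is wider than it need be. It also leaves in the estimate whatever difference in pre-brace quality of life the randomisation happened to produce. In a small trial without stratification that difference need not be small.

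H3 is the only hypothesis on a patient-reported outcome, and its conclusion depends on whether one end of a confidence interval clears a margin. Lost precision makes a truly non-inferior brace harder to demonstrate. A chance imbalance at Visit 1 can move the estimate towards or away from the margin for reasons unrelated to the brace.

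**Working it through.** **Inputs from the Protocol.** 25 evaluable patients per arm, 29 randomised (section 8.1). 95% confidence interval for the score difference (section 8.5), which amounts to a one-sided 2.5% test. Margin 10% with no stated base (section 4).

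**Inputs assumed.** The Protocol gives no SRS-22r SD and no correlation r between the Visit 1 and follow-up scores. The margin is therefore expressed in SD units from 0.5 to 1.0, and r is taken as 0.3, 0.5 and 0.7. The true difference is set to 0 and the SD is taken as equal at both times.

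**Step 1. The Protocol's own figure.** For H1, n per group = 2(z₁₋α + z₁₋β)²(σ/δ)². With σ = 7°, δ = 5°, one-sided α = 5% and power 80%, this is 2 × (1.645 + 0.842)² × 49/25 = 24.2, so 25. Then 25 × 1.15 = 28.75, so 29 per group and 58 in total. The stated size reproduces. It is for H1; there is no corresponding figure for H3.

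**Step 2. What the missing covariate costs.** With the Visit 1 score as covariate, the residual variance is SD² × (1 − r²).

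| r | Residual variance multiplier, 1 − r² | CI width multiplier, √(1 − r²) | Extra variance if unadjusted, 1/(1 − r²) − 1 | 25 per arm adjusted is worth, 25/(1 − r²) |
|---|---|---|---|---|
| 0.3 | 0.91 | 0.95 | 10% | about 27 |
| 0.5 | 0.75 | 0.87 | 33% | about 33 |
| 0.7 | 0.51 | 0.71 | 96% | about 49 |

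**Step 3. Power for H3.** Non-central t, 25 per arm, one-sided 2.5%. The non-centrality is (margin/SD) / [√(1 − r²) × √(2/25)], with 48 degrees of freedom unadjusted and 47 adjusted.

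| Margin in SD units | As written | r = 0.3 | r = 0.5 | r = 0.7 |
|---|---|---|---|---|
| 0.5 | 41% | 44% | 52% | 68% |
| 0.6 | 55% | 59% | 67% | 83% |
| 0.714 | 70% | 74% | 81% | 93% |
| 0.8 | 79% | 83% | 89% | 97% |
| 1.0 | 93% | 95% | 98% | 99.8% |

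The 0.714 row is the H1 ratio 5/7, shown only as a point of reference; it has no bearing on the questionnaire. Over the table the gain is about 2 to 4 points at r = 0.3, 5 to 12 at r = 0.5 and 6 to 28 at r = 0.7.

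These figures charge ANCOVA one degree of freedom but not the small variance cost of adjusting for the imbalance that actually occurs. That cost averages 1/(2 × 25 − 4) = 1/46, about 2% of the variance. Averaging over it lowers each adjusted power by less than one point.

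**Step 4. Chance imbalance.** The difference in mean Visit 1 score has standard error √(2/25) = 0.28 SD, so its 95% range is 1.96 × 0.28 = ±0.55 SD. The unadjusted comparison carries r times the observed baseline difference into the estimate. At r = 0.5 that is up to about 0.5 × 0.55 = ±0.28 SD, nearly half of a margin of 0.6 SD.

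**The case against.** The strongest reply has four parts.

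1. **Section 8.5 is a short template, not a full model.** Naming an outcome and an exposure does not exclude covariates, and adjustment of a secondary endpoint is often left to a separate statistical analysis plan. Such a plan could indeed add the covariate. But chapter 8 is itself titled as the statistical analysis plan, and section 8.5 gives the outcome, the independent variable, the interval and the decision rule. Read as written, baseline is not in it. Section 8.3 at least speaks of a difference in correction, which implies a starting value; section 8.5 has no such reference.
2. **The unadjusted comparison is valid.** This stands. Under randomisation the type I error is kept on average, and the 95% interval already allows for chance imbalance. The point is lost precision and an estimate that depends on the imbalance that happens to occur, not bias.
3. **The size is unknown.** This also stands. The SD, the correlation and the base of the 10% are all missing, and the gain could be only a few points.
4. **No power was promised for H3.** Correct, so no stated figure is contradicted. It also means that H3 has no planned reserve of precision to give away.

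Together these points limit the importance of the matter. They give no reason to prefer the unadjusted comparison when the covariate is collected anyway.

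**Conclusion.** The concern holds, as a matter of efficiency and not of validity. The H3 comparison as described leaves out a pre-brace measurement of the same outcome that is planned for every patient. It should be corrected, but H3 is secondary and the trial's main conclusion does not depend on it.

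The size rests on two quantities that the Protocol does not give. At a correlation of about 0.5 and a margin of 0.8 SD or less, the loss is 10 to 12 points of power, equivalent to having 25 patients per arm instead of about 33. At a correlation of 0.3, or with a margin near 1 SD, it is 5 points or less except where a correlation near 0.7 goes with the 1 SD margin (6 points).

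**What to change.** In section 8.5, state that each SRS-22r score at 1 and 2 years will be analysed by ANCOVA with randomised brace type and the Visit 1 value of the same score as covariates, and that the 95% confidence interval of the adjusted difference will be compared with the margin. Convert the 10% to score points, so that the margin is on the same scale as that interval; this is needed with or without adjustment.

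A simple change from baseline is not an equal substitute. Its variance is 2(1 − r) × SD², that is 1.4, 1.0 and 0.6 times SD² at r = 0.3, 0.5 and 0.7, against 0.91, 0.75 and 0.51 for ANCOVA. At r = 0.5 it gains nothing over the follow-up score alone, and at r = 0.3 it is worse.

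The cost is one sentence and one degree of freedom, with no new data, visits or patients. Naming the covariate before outcome data are seen also removes any later choice between adjusted and unadjusted results.

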#### 8.6. Analysis of secondary hypothesis H4

A statistical analysis will initially be completed to verify that there is no residual effect in the crossover design of the study. The analysis of secondary hypothesis H4 will have the Cobb angle while wearing the brace as the dependent variable and the type of brace as the independent variable. The 95% confidence interval of the difference in score between the test brace and the control brace will be constructed and compared to the non-inferiority margin.

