## **6. Methodology**

### **6.1. Study design**

A prospective, double-blind, non-inferiority, controlled and randomized clinical trial will be conducted to assess the effectiveness of a new orthopedic brace design platform. Fifty-eight patients will be recruited at the CHU Ste-Justine orthopedic clinic. The study will be divided into two phases. The first phase will use a crossover design to assess the immediate correction of both types of brace. The second phase will use a parallel design with a 1:1 allocation to assess the mid-term correction.

In phase 1, each patient will try on each type of brace with a “control: test” or “test: control” trial sequence. Immediate correction in braces will be assessed. During phase 2 each patient will use one of the two types of braces for a period of two years. There will be a renewal of the brace after 6 or 12 months based on updated spine x-rays and a new trunk geometry. This is in order to consider the growth of the patient and the inherent changes in the patient's body and the scoliotic deformity. Taking into account that all patients do not follow the same growth, renewal of the brace may sometimes be necessary before 12 months (for example after 6 months following a rapid growth spurt). In this case, the brace will be renewed before the end of 12 months to ensure adequate follow-up of the treatment by the patient. If the patient is part of the test group, the optimization of the correction will be redone.

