### **Visit 2: Cross-testing of the braces and delivery of the brace in the medium term**

During Visit 2, each patient will sequentially try on both braces. This corresponds to phase #1 (crossover design) of the study mentioned in section 6.1. The following interventions will be made:

The first brace will be delivered, and the location of the corrective supports, the overall conformation of the brace and the tension of the straps will be checked by the orthotist for the control brace and for the test brace. Neither the orthopedist nor the orthotist can modify the corrective effect of the test brace in their adjustments. The same manipulations will then be repeated with the second brace in the randomization sequence.

A digital x-ray will be taken in a supine position with the patient in a comfortable position, with the hips and knees extended, the hands in a lateral position relative to the head. The Cobb angle will be measured by an evaluator blind to the aims of the study. The same manipulations will then be repeated with the second brace in the randomization sequence.

- The patient will receive the brace corresponding to the group assigned to him by the randomization for phase #2. He will also receive the usual instructions for wearing the brace, unless he meets a failure criterion (see section 6.5).

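### Section 8.6 puts a residual-effect check ahead of H4 that is too weak to show what it is meant to show, and does not specify a within-patient analysis of the crossover

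*Protocol*

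**What the plan says.** H4 (section 4) is a secondary non-inferiority hypothesis: "The immediate in-brace correction of the Cobb angle of the Test brace will be no less than that of the control brace". Its margin: "The non-inferiority margin will be 5 degrees". The data come from phase 1. Section 6.1 states: "The first phase will use a crossover design to assess the immediate correction of both types of brace". Under Visit 2 in section 6.4, "each patient will sequentially try on both braces", with an X-ray in each, and section 7 randomises the order 1:1.

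Section 8.6 sets out the analysis in three steps:

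- a preliminary step: "A statistical analysis will initially be completed to verify that there is no residual effect in the crossover design of the study";
- the variables: "the Cobb angle while wearing the brace as the dependent variable and the type of brace as the independent variable";
- the inference, judged against the 5° limit of H4: "The 95% confidence interval of the difference in score between the test brace and the control brace will be constructed and compared to the non-inferiority" […].

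Section 8.6 names no test or significance level for the preliminary step and does not say what follows if a residual effect is found. It does not mention patient, period or sequence. The second and third steps follow almost the same template as section 8.5 (H3), a parallel-group comparison. They even keep the term score, although the H4 outcome is an angle.

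**The concern.** The preliminary step asks the data to establish that something is absent. In a two-by-two crossover a carry-over difference between the braces cannot be separated from a difference between the two sequence groups. It has to be tested on each patient's total over both periods, so it carries the full between-patient variation. Such a test is weak, and reading a non-significant result as confirmation mistakes lack of evidence for evidence of absence.

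Because no consequence is stated, a positive result would leave the H4 analysis to be chosen after the data are seen. The familiar choice, falling back on the first period, is known to distort the error rate, because the first-period comparison is correlated with the check that triggered it.

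The second strand is the model description. The value of phase 1 is that every patient wears both braces, and section 8.6 does not write that into the analysis. H4 is also measured before the change of brace group allowed in section 6.5 can take effect, so it deserves a clear specification.

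**Working it through.** **Inputs.** From the protocol: N = 58 (29 per sequence under 1:1 allocation), H4 margin 5°, two-sided 95% interval. SD 7° is given in section 8.1 for H1 and is assumed here to apply to the in-brace angle. The within-patient correlation ρ is not given; 0.5 to 0.9 is assumed. All 58 patients are taken to have both Visit 2 images.

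**The plan's own figure.** The protocol gives no sample size or power for H4. Its H1 figure reproduces at one-sided 5%: 2 × (1.645 + 0.842)² × 7² / 5² = 24.2, so 25 per group, and 25 × 1.15 = 28.75, so 29. The SD is therefore being read as intended.

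**1. Power of the residual-effect check.** The SD of a patient's two-period total is 7√(2(1+ρ)). The standard error of the difference between sequences is that SD × √(4/58). Power is from the noncentral t with 56 degrees of freedom.

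| ρ | SE | 5° carry-over, 5% level | 5°, 10% level | 2.5°, 5% level | 2.5°, 10% level |
|---|---|---|---|---|---|
| 0.5 | 3.18° | 34% | 46% | 12% | 20% |
| 0.7 | 3.39° | 31% | 43% | 11% | 19% |
| 0.9 | 3.58° | 28% | 40% | 11% | 18% |

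With 50 patients instead of 58, power for 5° at the 5% level falls to 25–30%.

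A carry-over difference of λ biases the within-patient brace difference by λ/2. So 5° of carry-over moves the H4 estimate by 2.5°, half the margin, and would be missed about two times in three. A bias equal to the whole margin needs λ = 10°. Then λ/SE is 10/3.18 = 3.14 at ρ = 0.5 and 10/3.58 = 2.79 at ρ = 0.9, and power at the 5% level is about 87% and 78%. The check can see a gross effect but cannot exclude a material one.

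**2. Error rate if the check switched the analysis.** The protocol states no fallback, so this step is conditional. Assume no carry-over and no brace difference, with a significant check leading to a first-period comparison and otherwise the within-patient comparison at two-sided 5%. Simulation (40,000 runs per setting, ρ 0.5, 0.7, 0.9) gives:

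- check at the 5% level: 7.6%, 7.8%, 8.4%;
- check at the 10% level: 8.0%, 8.7%, 9.4%;
- within-patient comparison without any check: 4.9–5.1%.

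Non-inferiority uses one side of the interval. By symmetry the one-sided error is half the two-sided figure: 7.6/2 = 3.8% to 9.4/2 = 4.7%, against 2.5%.

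**3. Effect of leaving out the pairing.** Paired half-width: t(56) × 7√(2(1−ρ)/58), with t = 2.003. Unpaired: t(114) × 7√(2/58) = 1.981 × 1.300 = 2.58°.

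| ρ | Paired | Unpaired | Ratio |
|---|---|---|---|
| 0.5 | 1.84° | 2.58° | 1.4 |
| 0.7 | 1.43° | 2.58° | 1.8 |
| 0.9 | 0.82° | 2.58° | 3.1 |

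If the braces are truly equal, power against 5° is at least 99.5% either way at these correlations. The unpaired one-sided error would be 0.25% or less instead of 2.5%.

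**The case against.** The case for leaving section 8.6 alone has real force on several points.

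- **The model.** A reader might infer that H4 will be analysed as two independent groups. The text does not say so. It names a dependent and an independent variable, uses similar wording for the other hypotheses, and calls the design a crossover. The interval of the difference could well be within-patient, and the full model may stand in an analysis plan that is not shown. This stands: the protocol leaves pairing unspecified; it does not reject it.
- **The error rate.** A reader might infer that type I error is inflated. That needs a decision rule and a first-period fallback, and the protocol has neither. If the check is only reported, no inflation arises. This stands, and the 8–9% must be kept conditional.
- **The consequence.** Even an unpaired half-width of 2.58° lies well inside the 5° margin, and the error would be on the conservative side. This stands.
- **The size of carry-over.** Nothing in the protocol suggests that 5° of carry-over is likely when two braces are fitted one after the other. This also stands: 5° is a yardstick for the check, not a forecast.

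None of this rescues the preliminary step itself. The protocol writes it in, gives its purpose as verification, and puts it before H4. A between-patient test of this size cannot serve that purpose, whatever is done with the result.

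**Conclusion.** The point holds in a limited form. The preliminary residual-effect check cannot verify absence: its power is about 28–34% at the 5% level (40–46% at 10%) for a carry-over difference of 5°, given SD 7° borrowed from H1, ρ between 0.5 and 0.9, and 58 complete pairs. That conclusion needs no assumption about what follows the check.

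Two parts are weaker. Inflation to about 8–9% two-sided applies only if a positive check switches H4 to the first brace, which the protocol does not state. The missing within-patient specification would cost precision if taken literally, but would be unlikely to change the H4 conclusion. H4 is secondary, so this is a minor-priority correction, worth making because it removes an unsound step at almost no cost.

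**What to change.** Rewrite section 8.6 as follows:

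1. Remove the residual-effect test as a condition for the H4 analysis. State instead why carry-over between the two fittings is expected to be negligible, by reference to the Visit 2 procedure in section 6.4. Deleting the test without this justification would leave carry-over unaddressed.
2. Prespecify one within-patient model: in-brace Cobb angle on brace and period, with patient as a fixed or random effect.
3. Compare the 95% confidence interval for the brace difference from that model with the 5° margin, whatever the period and sequence results show. Report the period effect and the between-sequence difference descriptively.
4. Refer to the difference in Cobb angle rather than in score.

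The cost is a few sentences in section 8.6. No extra patients, images or visits are needed.
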